## Abstract

**Background:**

The efficacy of attentional bias modification (ABM) as a treatment for anxiety and depression has been extensively studied with promising results. Despite some evidence of sleep-related attentional biases in insomnia, only a small number of studies, yielding mixed results, have examined the application of ABM in insomnia. This study specifically aims to determine whether ABM can reduce (i) the presence of an attentional bias for sleep-related threatening words; (ii) insomnia symptom severity; (iii) sleep onset latency; and (iv) pre-sleep cognitive arousal amongst individuals with insomnia compared to a non-treatment control group of individuals with insomnia.

**Methods/design:**

We propose a randomised controlled trial of 90 individuals from the general population who meet the criteria for Insomnia Disorder. Following an initial examination for the presence of a sleep-related attentional bias using the dot-probe paradigm, participants will be randomised to an online attentional bias modification training condition, or to a standard attentional bias task (non-treatment) control condition. Both conditions will be delivered online by a web platform. All participants allocated to the non-treatment control group will be offered ABM training once the study is complete. The primary outcome will be the attentional bias indices of vigilance and disengagement and self-reported insomnia symptoms, sleep onset latency and pre-sleep cognitive arousal. Attentional bias and insomnia symptoms will be assessed at baseline (day 1) and post-treatment (2 days after the final training session: day 9). Insomnia symptoms will be again assessed at follow-up (day 16). Secondary outcomes include examining whether sleep associated monitoring and worry are related to a sleep-related attentional bias in insomnia, and whether such reports reduce following ABM. All main analyses will be carried out on completion of follow-up assessments. The trial is supported by the Department of Psychology, Sociology and Politics at Sheffield Hallam University.

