### Participants and recruitment

We will recruit a total of 90 adult members from the general population who meet the *Diagnostic and Statistical Manual of Mental Disorders, 5*^*th*^
*edition* (DSM-5) criteria for Insomnia Disorder [19]. Potential participants will be recruited through the website ‘call for participants’ and various insomnia treatment forums and will be assessed online for eligibility. Those interested in taking part will complete the Insomnia Severity Index (ISI: [20]), and SLEEP-50 [21] measures (see ‘Questionnaire Measures’ section for more detail). Those indicating subclinical insomnia using the ISI, and do not indicate the presence of another sleep/wake disorder other than insomnia on the SLEEP-50 will be invited for a telephone interview to determine the presence of DSM-5 Insomnia Disorder. Telephone interviews will be conducted by the principal investigator (UA).

Specifically, individuals with insomnia must report dissatisfaction with sleep characterized by either a difficulty initiating or maintaining sleep or early morning awakenings. Insomnia should be present for 3 or more nights per week, for at least 3 months, and cause significant daytime impairment. Finally, these conditions must be met despite an adequate opportunity to sleep. Those who report symptoms of a sleep/wake disorder other than insomnia, an existing psychiatric illness, a central nervous system disorder, use of medication that may affect sleep, a prior head injury, pregnancy or breast-feeding or current shift-work will be ineligible to take part. Those meeting the criteria for Insomnia Disorder will be invited to participate and will be provided with an email link for the online study. All participants must have normal to corrected vision.

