### Randomisation and allocation concealment

This study will use a simple randomisation with an allocation ratio of 1:1 which will be carried out by the automated online system. As such, the research team will not be able to influence randomisation and will not have access to future allocations.

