#### Sample size rationale

The current power estimation was based on the meta-analysis on ABM training for anxiety conducted by Hakamata and colleagues [27] who noted a mean effect size equal to Cohen’s *d* = .61. In each group, we would require 44 participants based on a *t* test, power of .80 and an alpha level of .05 (two-tailed).

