##### Analyses

First, we will examine group differences in attentional bias indices at baseline with the expectation that there should be no group difference. Following this, we will examine differences in attentional bias indices at follow-up (i.e. day 9). To examine whether any attentional bias reduced amongst the experimental group, we will then examine the group (experimental versus control) × time (baseline versus post-ABM) interaction for each index of attentional bias (i.e. vigilance and disengagement). Second, to examine whether insomnia symptoms reduced amongst the experimental group, we will examine the group (experimental versus control) × time (baseline versus post-ABM versus follow-up) interaction. Third, to separately examine whether pre-sleep cognitive arousal and sleep-onset latency reduced amongst the experimental group on nights where the tasks were completed, we will examine the group (experimental versus control) × time (days 3 vs. 4 vs. 5 vs. 6 vs. 7) interactions. Finally, to explore the secondary aim we will employ a series of Pearson’s correlational analyses to determine whether each of the attentional bias indices (i.e. vigilance and disengagement) are related to each subscale of the SAMI. Simple effects analyses will be performed to decompose any significant interactions as appropriate.

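### Five outcomes are named as primary with no order, success rule or alpha adjustment, while the sample size is for one t test tied to none of them

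*Protocol article*

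**What the plan says.** The abstract (Methods/design) defines the primary outcome in one sentence: "The primary outcome will be the attentional bias indices of vigilance and disengagement and self-reported insomnia symptoms, sleep onset latency and pre-sleep cognitive arousal". The body agrees. The Background lists four unranked aims, the first covering both bias indices, and the Questionnaire measures section puts the Insomnia Severity Index (ISI), the sleep diary measure of sleep onset latency (SOL) and the Pre-Sleep Arousal Scale together as primary measures.

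The Analyses section plans a separate group × time interaction for vigilance, disengagement, ISI, SOL and pre-sleep arousal. For the two bias indices it adds a between-group comparison after training: "we will examine differences in attentional bias indices at follow-up (i.e. day 9"). It states no significance level, no order of testing and no rule for how many outcomes must succeed.

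The only alpha is in the Sample size rationale, which uses "power of .80 and an alpha level of .05 (two-tailed"). The effect size is one figure from outside insomnia: "The current power estimation was based on the meta-analysis on ABM training for anxiety", which "noted a mean effect size equal to Cohen’s *d* = .61". The result is 44 per group from a t test, and the outcome being tested is not named. Planned recruitment is 90, with "simple randomisation with an allocation ratio of 1:1", so 45 per group is expected.

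**The concern.** The list of primary outcomes and the sample size do not fit together. A calculation for one test at .05 describes a trial with one primary test. With five, the .05 is the error rate of each test, and the trial's own error rate depends on a success rule that the plan does not give.

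This matters because the five outcomes support different claims. A change in a bias index shows that the training altered performance on the dot-probe task. It does not show that insomnia improved, which is the therapeutic question in the Background. As written, a significant result on either kind of outcome could be reported as a primary success, and nothing fixed in advance says which one the trial was designed to test.

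**Working it through.** **Inputs.** From the protocol: five primary outcomes (abstract); d = .61, alpha .05 two-sided, power .80 and 44 per group (Sample size rationale); 90 in total, so 45 per group (Participants and recruitment; Randomisation). Assumed: each outcome is tested at .05, the only alpha given; the five tests have a common correlation ρ. The protocol gives no correlation, so a range is shown.

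**1. The plan's own figure.** For a two-sample t test with n per group, the noncentrality is d√(n/2). Solving for power .80 at two-sided .05 with d = .61 gives n = 43.17, rounded up to 44. The stated figure is reproduced for one test. Power is .808 at 44 per group. At 45 per group the noncentrality is .61 × √22.5 = 2.89 and power is .816.

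**2. Family-wise error, five tests at .05, all nulls true, any one significant result counting, either direction.**

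- Independent: 1 − .95⁵ = .226. The Bonferroni upper bound is 5 × .05 = .25.
- Equal correlation, from 400,000 simulated sets of two-sided z tests:

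| ρ | Either direction | Favouring the training only |
|---|---|---|
| 0 | 22.6% | 11.9% |
| .3 | 20.9% | 10.5% |
| .5 | 18.3% | 9.2% |
| .7 | 14.9% | 7.5% |
| .9 | 10.2% | 5.2% |

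The one-directional figure under independence is 1 − .975⁵ = .119; the benchmark for a single test is .025. If the two bias indices are counted as one aim, four independent tests give 1 − .95⁴ = .185.

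**3. Power if the error rate is controlled across all five.** Bonferroni, and the first step of Holm, use .05/5 = .01. With d = .61, power is .591 at 44 per group and .604 at 45. Reaching .80 at alpha .01 needs n = 64.45, so 65 per group or 130 in total, against 90 planned.

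**4. Power if all five had to succeed.** Each test could then stay at .05 with the error rate controlled. But with .816 per outcome and independence, the power for all five is .816⁵ = .36. Positive correlation would raise this.

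The stated .80 therefore fits one primary test, or the first test in a fixed sequence. It fits neither Bonferroni/Holm over five nor success on all five under independence.

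**The case against.** The strongest reply is that this is a condensed article, that multiplicity handling is commonly left to an analysis plan, and that the Analyses section never says each outcome is tested at .05. That stands in part: the .05 per test is inferred, and silence about an adjustment is not the finding. What remains is what the article does state, namely five undifferentiated primary outcomes and a sample size for one unnamed test. A later Holm or Bonferroni adjustment would not agree with the alpha behind that sample size.

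A second reply is that the four aims are separate questions, and whether separate aims form one error family is a matter of judgement. That is fair, and the protocol nowhere says that any single significant result is success. But it gives no other rule either, and it calls the whole set the primary outcome.

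Some stronger readings are tempting and are not supported:

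- **A 1-in-5 chance of wrongly claiming that the training works.** A reader might infer this from 22.6%. That figure counts results in either direction. For results favouring the training it is about 12% under independence, and less with positive correlation.
- **Seven confirmatory tests and an error of 30.2%.** This adds the two day-9 bias comparisons and uses 1 − .95⁷. Those comparisons share the day-9 data with the interactions, so they are not independent of them, and the protocol presents the interaction as the test of whether bias was reduced.
- **Power of .80 lost under any valid correction.** A fixed sequence is valid and keeps .05, hence .816 with 45 per group, for its first outcome.
- **Power of .60 as the power of Holm.** It is the first-step floor for one given outcome. Later steps use a larger alpha if other outcomes are rejected first.
- **ISI as the evident primary outcome.** The protocol calls SOL the critical measure. The ISI recall period is two weeks, so on day 9 it reaches back before the training on days 3 to 7. The choice belongs to the investigators.

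**Conclusion.** The point holds. The protocol fixes five primary outcomes with separate tests and no order, success rule or adjustment, and it justifies the sample size by a single test that is tied to none of them.

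Its size is conditional. The family-wise error of 22.6% (about 18 to 21% at moderate correlation, about 15% at .7) needs testing at .05 each, all nulls true, and any one result counting in either direction. Under the mildest setting in the table, ρ = .9, it is still about twice the nominal rate. The power of about .60 is a worst case at alpha .01, and it takes d = .61 and the t test at face value; the planned tests are interactions, and dropout is not allowed for. Those are separate questions and are not needed for this conclusion.

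**What to change.** Before data collection starts (Trial status gives 1 November 2018), the investigators should choose one of two routes and write it into the outcome, sample size and analysis sections.

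- **One primary outcome or a fixed order.** Name one primary outcome with one contrast and one time point, tested at .05, or state a fixed order in which the outcomes are tested. Tie d = .61 and the 44 per group to the first or only outcome by name. With a single primary, make the other four secondary.
- **Keep all five.** Pre-name one test per outcome, the group × time interaction, and apply Holm across the five. Make the separate day-9 bias comparisons supportive. Restate power as about .60 at the first step with 45 per group, or plan for 65 per group if .80 is wanted there.

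The first route changes no numbers, but with a single primary four outcomes lose primary status. Because the trial is already registered and recruiting, the registered outcomes need updating with a dated reason. The second keeps all five outcomes primary at the price of less favourable stated power or a larger trial.

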**Discussion:**

This study will extend the research base examining the efficacy of attentional bias modification for insomnia.

**Trial registration:**

ISRCTN (ISRCTN11643569, registered on 5 June 2018).

Recent research has examined the efficacy of delivering ABM immediately prior to bed as a treatment for individuals reporting elevated disposition to experiencing poor sleep quality [16, 17]. Specifically, these studies obtained evidence that individuals provided with ABM also reported improved subjective sleep quality, reduced pre-sleep arousal, and reduced sleep onset latency relative to control conditions where a standard attentional bias task was delivered. However, these studies utilised a measure of disposition to experiencing poor sleep to recruit participants, rather than a measure of disposition to experiencing insomnia-specific symptoms, which limits the generalisability of these studies. To that end, Lancee et al. [18] explored the therapeutic effect of ABM amongst those meeting diagnostic criteria for insomnia. Whilst no therapeutic effects were observed in this study, ABM was administered in the evening between 7 and 11 pm, rather than immediately prior to bed when biased attention may be most prominent [16].

The present research aims to further examine the therapeutic potential of attentional bias modification for the treatment of insomnia-specific symptoms. Previous research has proved to be efficacious where delivery of ABM and control tasks are alternated amongst the same sample [16]. Whilst this research highlights promising outcomes for those experiencing sleep disturbance, these outcomes cannot be extrapolated to individuals with insomnia. Moreover, the within-subjects alternating nature of this research may also prevent any potential accumulation of improved sleep from being otherwise observed. Therefore, the current study will implement a between-subjects design using a sample of individuals meeting the diagnostic criteria, who will be randomly allocated to either a treatment or non-treatment control condition. This will allow for observation of ABM over repeated nights and for the presence of any potential cumulative changes in outcome measures. Specifically, using a similar modified dot-probe task to Milkins et al. [16], we aim to determine whether ABM can reduce (i) the presence of an attentional bias for sleep-related negative words characterised by either vigilance (i.e. speeding of attention towards salient stimuli) or disengagement (i.e. difficulty in shifting attention away from salient stimuli); (ii) insomnia symptom severity; (iii) sleep onset latency; and (iv) pre-sleep cognitive arousal amongst individuals with insomnia compared to a non-treatment control group of individuals with insomnia. As a secondary aim, we also seek to determine whether initial attentional bias is related to greater self-reports of sleep-associated monitoring behaviour and sleep-related worry, and whether such reports reduce following ABM.

## Methods/design

### Trial design

This study is a double-blind randomised controlled trial examining the efficacy of ABM for insomnia delivered over the internet (see Fig. 1. for summary). The study has received ethical approval from the Sheffield Hallam University Research Ethics Committee (reference number: ER5451619).

**Fig. 1 Fig1:**
[figure not shown]
Flow chart diagram showing the summary of the trial design. *DSM-5* Diagnostic and Statistical Manual of Mental Disorders, 5^th^ edition, *ISI* Insomnia Severity Index

### Participants and recruitment

We will recruit a total of 90 adult members from the general population who meet the *Diagnostic and Statistical Manual of Mental Disorders, 5*^*th*^
*edition* (DSM-5) criteria for Insomnia Disorder [19]. Potential participants will be recruited through the website ‘call for participants’ and various insomnia treatment forums and will be assessed online for eligibility. Those interested in taking part will complete the Insomnia Severity Index (ISI: [20]), and SLEEP-50 [21] measures (see ‘Questionnaire Measures’ section for more detail). Those indicating subclinical insomnia using the ISI, and do not indicate the presence of another sleep/wake disorder other than insomnia on the SLEEP-50 will be invited for a telephone interview to determine the presence of DSM-5 Insomnia Disorder. Telephone interviews will be conducted by the principal investigator (UA).

Specifically, individuals with insomnia must report dissatisfaction with sleep characterized by either a difficulty initiating or maintaining sleep or early morning awakenings. Insomnia should be present for 3 or more nights per week, for at least 3 months, and cause significant daytime impairment. Finally, these conditions must be met despite an adequate opportunity to sleep. Those who report symptoms of a sleep/wake disorder other than insomnia, an existing psychiatric illness, a central nervous system disorder, use of medication that may affect sleep, a prior head injury, pregnancy or breast-feeding or current shift-work will be ineligible to take part. Those meeting the criteria for Insomnia Disorder will be invited to participate and will be provided with an email link for the online study. All participants must have normal to corrected vision.

### Randomisation and allocation concealment

This study will use a simple randomisation with an allocation ratio of 1:1 which will be carried out by the automated online system. As such, the research team will not be able to influence randomisation and will not have access to future allocations.

### Blinding

This will be a double-blind trial. Once invited to participate, all assessments and group allocation will occur online, and the research team will be blind to outcomes during the trial. Participants will not be aware whether they are in the experimental or control condition. It is relevant to note that the research team is unlikely to have any contact with the participants, and as such it will be unlikely that they are able to bias allocation or assessment.

### Word pairs

#### Assessment pairs

In this study we will use the same set of 48 sleep-negative and neutral word pairs as used by Milkins et al., ([16]; see Tables 1 and 2 for word pairs). A subset of 24 of these sleep-negative and neutral word pairs will be used alongside 24 neutral-neutral word pairs. Each of the words will be matched on frequency and length.

**Table 1 Tab1:** List of sleep-negative/neutral and neutral-neutral word pairs for attentional bias assessment points (baseline and post-treatment)

Sleep-negative and neutral pairs		Neutral-neutral pairs	
Sleep-negative word	Matched neutral word	Neutral word	Matched neutral word
Ache	Melt	Graft	Males
Lethargy	Teaspoon	Featuring	Scrubbing
Agitated	Carriers	Cushion	Specify
Naps	Kits	Meals	Chord
Angry	Curve	Led	Lot
Overactive	Clearances	Stairs	Mirror
Coffee	Beside	Invoice	Prodigy
Sleepy	Wallet	Playful	Tramped
Delirious	Fragments	Margin	Pencil
Snoring	Penguin	Tops	Laps
Disastrous	Curriculum	Book	News
Tense	Trick	Habit	Steel
Disorder	Compost	Sandals	Potters
Sluggish	Decorate	Attendants	Speculates
Distress	Creature	Invents	Drafted
Restless	Receiver	Graft	Disarm
Exhausted	Developed	Point	Water
Snoring	Penguin	Thankful	Entrants
Hopeless	Borrowed	Vaccine	Embrace
Sleepy	Wallet	Wriggles	Fixation
Inadequate	Initiative	Pear	Bath
Nightmare	Volunteer	Trait	Stand
Irritable	Appliance	Days	Motel
Drowsy	Umpire	Eraser	Places

**Table 2 Tab2:** List of sleep-negative/neutral word pairs for ABM experimental and control conditions

Sleep-negative and neutral pairs		Neutral-neutral pairs	
Sleep-negative word	Matched neutral word	Sleep-negative word	Matched neutral word
Ache	Melt	Lazy	Hint
Afraid	Artist	Lethargy	Teaspoon
Agitated	Carriers	Medication	Bottleneck
Alarm	Spray	Naps	Kits
Angry	Curve	Nightmare	Volunteer
Anxiety	Express	Overactive	Clearances
Coffee	Beside	Panicky	Infuser
Conflict	Advanced	Restless	Receiver
Delirious	Fragments	Sad	Cup
Desperate	Aesthetic	Sick	Pull
Disastrous	Curriculum	Sleepless	Advisable
Disengaged	Nonfiction	Sleepy	Wallet
Disorder	Compost	Sluggish	Decorate
Distract	Brochure	Snoring	Penguin
Distress	Creature	Stress	Links
Drowsy	Umpire	Suffer	Branch
Exhausted	Developed	Tense	Trick
Fatigue	Passive	Time	Look
Hopeless	Borrowed	Tired	Plain
Illness	Mustard	Unpleasant	Expedition
Inadequate	Initiative	Wakeful	Trolley
Irrational	Flashlight	Work	Life
Irritable	Appliance	Workload	Handbags
Jittery	Thermos	Worry	Theme

*ABM* attention bias modification

#### ABM control and experimental pairs

Here, we will use the full set of 48 sleep-negative and neutral word pairs as used by Milkins et al., [16].

### Questionnaire measures

#### Primary measures

##### Insomnia severity

Insomnia symptoms will be assessed using the Insomnia Severity Index [20] (ISI). The ISI consists of seven items examining the severity of insomnia symptoms over the past 2 weeks including difficulty initiating and maintaining sleep and awakening too early. Items are scored on a 5-point Likert scale, with total scores ranging from 0 to 28. Higher scores represent greater insomnia severity, with scores of ≥ 8 indicative of subclinical insomnia.

##### Consensus sleep diary

The critical measure of sleep onset latency (SOL) will be assessed as part of a standardized sleep diary [22], completed by participants each morning of the study. Here, participants will record in minutes the estimated time taken to fall asleep the previous night.

##### Pre-sleep cognitive arousal

To assess pre-sleep cognitive arousal before and after delivery of the ABM/control tasks, we will use the Pre-Sleep Arousal Scale (PSAS: [23]). The scale contains 16 items related to the kinds of thoughts and sensations experienced in the pre-sleep period which can contribute to sleeplessness.

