**Fig. 2 Fig2:**
[figure not shown]
Example order of individual trial sequence for the dot-probe task. Fixation cross first presented for 500 msec, followed by word presentation side-by-side for 500 ms. After 100 ms interval, probe appears until response. If the corresponding probe location key (i.e. correct response) was pressed, no feedback is presented, and the next trial begins after 500 ms blank screen interval. However, incorrect response feedback is presented if the wrong key is pressed triggering a 3000 ms interval before the next trial begins

The modified ABM version of the task will consist of 10 repetitions of 48 word pairs delivered in randomised blocks (all sleep-negative/neutral). Here, the probe always replaces the locus of the neutral word, promoting attentional avoidance of sleep-negative stimuli. In the non-ABM control condition, all task parameters are identical to the modified ABM version, however the probes replaced the negative and neutral member of each word pair with equal frequency without promoting attention toward or away from negative words.

Following this, participants will complete: the ISI, SAMI, ASPQ, and SAAQ.

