##### ABM intervention and control group procedure

On days 3–7, using a computer, participants will be required to complete a dot-probe task prior to bed. The nature of the dot-probe task will depend on group allocation. Those in the experimental treatment condition will be provided with a modified version of the aforementioned dot-probe task such that the probe only appears in the location of the neutral word. Theoretically shifting (training) their attention away from the sleep-negative words. Whereas those in the control condition will complete the same task with probes replacing the negative and neutral member of each word pair with equal frequency. Following the task, participants will complete the Pre-Sleep Arousal Scale prior to bed. On awakening, participants will be required to complete an online version of the consensus sleep diary.

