##### Post ABM assessment and questionnaire measures

Following this 5-per week protocol, all participants will the complete the same attentional bias task (as completed at baseline) on the final day of the experimental phase (day 9). Moreover, the same questionnaire measures (ISI, SAMI, ASPQ, SAAQ) and sleep diary will also be completed.

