##### Follow-up assessment

At follow-up (day 16) participants will again complete the ISI, SAMI, ASPQ and SAAQ. On completion, participants will be provided with an Amazon e-gift voucher for taking part. Moreover, those in the control condition will be invited to take part in the experimental treatment if willing.

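### The protocol conflicts on whether the PSAS is taken before the task; on the post-task-only schedule there is no untreated value, and the days 3–7 interaction cannot detect an effect already complete on day 3

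*Protocol article*

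**What the plan says.** The abstract of the protocol article lists the primary outcomes as the two attentional bias indices together with "self-reported insomnia symptoms, sleep onset latency and pre-sleep cognitive arousal". Cognitive arousal is therefore one primary outcome among several.

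The subsection on pre-sleep cognitive arousal, under the primary measures, names the PSAS. It states the purpose as "To assess pre-sleep cognitive arousal before and after delivery of the ABM/control tasks" and describes the content: "The scale contains 16 items related to the kinds of thoughts and sensations experienced in the pre-sleep period". It does not say which items form the outcome score.

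The section on the ABM intervention and control group procedure, which covers days 3–7, places the scale once per night: "Following the task, participants will complete the Pre-Sleep Arousal Scale prior to bed".

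The other assessment points do not list the PSAS:
- Day 1: "Following this, participants will complete: the ISI, SAMI, ASPQ, and SAAQ".
- Day 9: "the same questionnaire measures (ISI, SAMI, ASPQ, SAAQ) and sleep diary will also be completed".
- Day 16: "At follow-up (day 16) participants will again complete the ISI, SAMI, ASPQ and SAAQ".

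The Analyses section sets out "to separately examine whether pre-sleep cognitive arousal and sleep-onset latency reduced amongst the experimental group", by a group × time interaction whose time factor has five levels, days 3, 4, 5, 6 and 7.

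**The concern.** The measures section promises a value before the task, and the procedure contains none. If sites and software follow the procedure, the first PSAS score in the trial is taken after the first ABM session.

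The analysis then asks whether arousal fell, using a time factor with no untreated level. A group × time interaction tests whether the group difference changes across days. If training lowers arousal on the first night and the difference then holds, nothing changes from day 3 to day 7 and the interaction is null.

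The protocol's own rationale makes this pattern plausible. The Background says that the immediate effects of ABM seem most marked when it precedes a threatening event, and it argues for delivery right before bed for that reason. The plan could therefore report no effect on a primary outcome in the case its rationale leads one to expect.

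A smaller, related gap is that the claim concerns cognitive arousal, the scale covers thoughts and sensations, and no score is named.

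**Working it through.** **1. The plan's own figure.** The sample size rationale gives d = .61, a two-sided alpha of .05, power of .80 and a t test, and arrives at 44 per group. The noncentral t calculation gives 43.17, which rounds up to 44, so the figure reproduces. Power is 80.8% at 44 per group and 81.6% at 45 per group (90 recruited, 1:1). The protocol expects dropout but gives no rate, so 45 per group is the best case.

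**2. Can the timing statements be reconciled?**
- If before and after means each night, the procedure contradicts it, because it gives the scale only after the task.
- If it means before and after the whole training period, the day 1 and day 9 lists contradict it, because neither includes the PSAS.

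On either reading, the pre-task value appears nowhere in the written schedule.

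**3. What the days 3–7 interaction can detect.** Inputs: n = 45 per group; an effect of 0.61 SD, borrowed from the sample size rationale; equal correlation ρ between days. The values ρ = .3, .5 and .7 are assumptions, because the protocol gives no PSAS variances or correlations. With δ_j the group difference on day j in SD units, the interaction has noncentrality

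λ = (n/2) × Σ(δ_j − mean δ)² / (1 − ρ), on 4 and 352 degrees of freedom.

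*Effect complete on day 3 and constant.* Every δ_j is .61, so the sum is 0 and λ = 0 for any ρ. The rejection rate is alpha.

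*Effect building linearly from 0 on day 3 to .61 on day 7.* The sum is 2 × (.305² + .1525²) = .2326. Then λ = 22.5 × .2326 / (1 − ρ) = 7.5, 10.5 and 17.4.

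*Comparison of five-day means.* The SD of a person's mean is √((1 + 4ρ)/5) = .663, .775 and .872. A constant .61 becomes d = .92, .79 and .70.

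Simulated rejection rates (4,000 runs per scenario):

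| Pattern of effect | Test | ρ = .3 | ρ = .5 | ρ = .7 |
|---|---|---|---|---|
| Constant .61 from day 3 | days 3–7 interaction | 4.9% | 4.5% | 4.0% |
| Constant .61 from day 3 | five-day mean | 99% | 96% | 91% |
| Linear, 0 to .61 | days 3–7 interaction | 56% | 71% | 93% |
| Linear, 0 to .61 | five-day mean | 57% | 45% | 38% |

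The noncentral F and t distributions agree with the non-null entries to within about two percentage points, and give 5% for the constant effect under the interaction.

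**4. What a pre-task level would restore.** Suppose the time factor has six levels, a pre-task value with δ = 0 and five post-task days at .61. The sum of squares is .61² × 5/6 = .310. Then λ = 22.5 × .310 / (1 − ρ) = 10.0, 14.0 and 23.3 on 5 and 440 degrees of freedom, and power is 67%, 83% and 98%.

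**5. The scoring question.** Assume two equal-variance halves (thoughts, sensations) correlated ρ, with .61 on the thought half. A summed total then has d = (.61 + d_sensation)/√(2(1 + ρ)). The halves and ρ are assumptions. Power is for a two-sample t test at 44 per group, ρ running from .3 to .7:

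| Effect on sensations | d of total | Power |
|---|---|---|
| none | .38 to .33 | 42% to 34% |
| half (.305) | .57 to .50 | 75% to 63% |
| equal (.61) | .76 to .66 | 94% to 87% |

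The thought items alone give 80.8%.

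**The case against.** **Randomisation makes a baseline unnecessary.** With 1:1 random allocation, a comparison of post-task scores between groups is valid without any pre-task value, so a reader should not infer that the post-task schedule leaves nothing to analyse. This stands. But the Analyses section does not name that comparison for the PSAS. It names the interaction, and simple effects only to follow up a significant one. A pre-task covariate alone would not help either if the tested term stayed the days 3–7 interaction.

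**The effect may build over nights.** The protocol says it wants to observe cumulative change, and for a linear build-up the interaction does as well as the five-day mean at ρ = .3 and better at .5 and .7. This also stands. The interaction is a fair test of accumulation and a blind one for an immediate effect.

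**The time points may be in a figure.** The flow chart and the SPIRIT figure are not shown and may list the PSAS. That could show which version is intended, but the two text sections would still disagree.

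**Scoring detail belongs elsewhere.** A condensed article often leaves scoring rules to the full protocol or analysis plan, and the two sleep-anxiety questionnaires are described without one as well. A reader might infer that all 16 items are summed and that the effect is therefore diluted. The text supports neither. It says what the scale contains, not what is scored, and the heading and the analysis both say cognitive. Dilution further needs ABM to affect sensations less than thoughts, whereas the Background links selective attention to physiological as well as cognitive arousal. With an equal effect on both, no power is lost.

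**Conclusion.** The point holds for timing and for the test that follows from it. The measures section and the procedure contradict each other on a primary outcome, and no reading of the text supplies the pre-task value. On the procedure's schedule, the planned interaction begins after the first session and rejects at about alpha (4–5%) for a constant 0.61 SD difference, when a comparison of five-day means would reject in 91–99%.

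The null result for the interaction follows from algebra and does not depend on ρ. The 91–99% depends on the assumed correlations of .3 to .7, on 45 complete participants per group and on borrowing .61 SD from the sample size rationale. If the effect builds linearly instead, the interaction has 56–93% power, so the loss is specific to an early effect.

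The scoring part is an unnamed score that is worth fixing in the same edit. It is not a demonstrated loss of power: the low figures (34–42%) require both a summed total and no effect on sensations.

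**What to change.** 1. Reconcile the measures section and the procedure by keeping the pre-task PSAS that the measures section already states, at least once before the first session on day 3.
2. In the Analyses section, either test the group difference in post-task PSAS averaged over days 3–7 with the pre-task value as covariate, or enter the pre-task value as a level of the time factor. Keep the days 3–7 interaction as the test of accumulation, not as the only test. State in advance which test carries the claim for this outcome.
3. Name the cognitive-item score as the outcome in the measures and analysis sections. The full scale can still be given, with the sensation items reported separately.

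The cost is protocol wording, a few lines of scoring and analysis code, and one short questionnaire before the day 3 session. The sample size and the intervention are unaffected. The change is easiest before data collection starts, which the protocol dates to 1 November 2018. If PSAS data already exist without a pre-task value, the unadjusted five-day mean comparison is still available and should be specified before unblinding.
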